### 3.2.5 Head and neck cancer

In the United States, there is an excess of approximately 50% in oral cavity cancer cases among PLWHA compared to the population. This excess increases to almost 70% among those living with AIDS for five or more years (BEACHLER *et al.*, 2014).

Warts are caused by low-risk HPV and are more prevalent among HIV-infected people, but their size may not correlate well with immunity (PERNOT *et al.*, 2014).

In the general population, HPV infection is considerably higher in young people and decreases with age (LEWIS *et al.*, 2018). Preliminary data from the POP-Brasil project – Epidemiological Study on the National Prevalence of HPV Infection showed that the estimated prevalence of HPV among young people aged 16 to 25 is 54.6% (POP-BRASIL, 2017). The prevalence profile for HPV-16 is 53.2% and 15.8% for HPV-18 (BRASIL, 2018).

According to data obtained from the Health Surveillance Secretariat, in 2018, 43,941 new cases of HIV and 37,161 cases of AIDS were diagnosed in Brazil.

Between 2008 and 2018, there was an increase in the detection rate among young people aged 15 to 19 and 20 to 24 years old of 62.2% and 94.6%, respectively. This group alone is estimated to have more than 115,000 people, considering the year of diagnosis between 2008 and 2018. Among women, there was a decrease in the detection rate in all age groups during the same period (BRASIL, 2019b). Compulsory notification of HIV infection began in 2014, which, added to the underreporting factor, makes it difficult to conduct a more rigorous epidemiological analysis of infection trends in Brazil.

### 3.3 THE HPV VACCINE

The first HPV vaccine ( vHPV ) was licensed in 2006 and many countries have since included it in their national immunization programs (WHO, 2016) . There are currently three prophylactic HPV vaccines on the market:

- i. The quadrivalent vaccine Gardasil (Merck Inc.): first licensed in 2006 and targets oncogenic HPV-16/18 as well as low-risk HPV-6/11 types that cause genital warts.
- ii. The bivalent vaccine Cervarix (GlaxoSmithKline): licensed in 2007, offers protection against HPV-16/18.
- iii. The nonavalent vaccine Gardasil 9 (Merck Inc.): licensed in 2014, provides protection against HPV-6/11/16/18 and five other more carcinogenic types (HPV-31/33/45/52/58) (MARTEL, *et al.* , 2017)

None of the vaccines contain live biological products or viral DNA and are therefore non-infectious; they do not contain antibiotics or preservatives. In addition to the viral types for which they are intended, they also differ in terms of indication and dosage. The vaccine is not recommended during pregnancy (WHO, 2017) .

After a 3-dose schedule, the quadrivalent and bivalent vaccines were evaluated and shown to be highly immunogenic, with the highest immune responses observed in girls aged 9 to 15 years (SCHILLER, CASTELLSAGUÉ and GARLAND, 2012) . Both confer protection for approximately 10 years (SCHWARZ *et al.* , 2019) . Evaluated in three Phase II/III studies, the quadrivalent vaccine showed seropositivity rates of 97.6%, 96.3%, 100% and 91.4% for HPV-6/11/16/18 types, respectively. (NYGÅRD *et al.* , 2015) . Regarding adverse effects, a meta-analysis that included 14

studies showed that the main adverse effects related to vaccination were pain, erythema, edema and fever (COELHO *et al.* , 2015) .

#### 1.1.1. Efficacy, safety and immunogenicity of the HPV vaccine in PLWHA

A study of quadrivalent vHPV in HIV-infected adolescents and young adults aged 13 to 27 years showed that the vaccine is safe and well tolerated, with a seroconversion rate of 85% in HIV-infected individuals and 91% in HIV-negative individuals. No serious or life-threatening adverse events were reported. The most common local side effect was pain, which occurred in 18.8% of HIV-negative patients and in 32.6% of HIV-infected patients. The most common systemic side effect was headache, reported in 13.5% of HIV-infected individuals and in 2.2% of HIV-negative individuals (GIACOMET *et al.*, 2014) .

The safety and immunogenicity of bivalent vcHPV in HIV-infected women in South Africa were also evaluated. vcHPV was found to be safe in asymptomatic HIV-positive women aged 18 to 25 years and no impacts on CD4 T-cell count, HIV viral load or HIV clinical stage were identified (DENNY *et al.*, 2013).

A study of 319 HIV-infected women in the United States, Brazil, and South Africa showed that quadrivalent vcHPV is safe and immunogenic in HIV-infected women aged 13 to 45 years. The seroconversion rates for the four HPV types (6, 11, 16, and 18) in women with CD4 T-cell counts greater than 350 cells/ $\mu$ L were 96%, 98%, 99%, and 91%, respectively, while women with CD4 counts of <200 cells/ $\mu$ L had conversion rates of 84%, 92%, 93%, and 75%, respectively (KOJIC *et al.*, 2014) . In a clinical trial of HIV-positive MSM vaccinated with three doses of quadrivalent vcHPV , seroconversion rates for all HPV types (6, 11, 16, and 18) were 98%, 99%, 100%, and 95%, respectively. No adverse effects on CD4+ counts or plasma HIV-1 RNA were observed. There were also no grade 3 or higher adverse events attributable to vaccination among the 109 men who received at least 1 dose of the vaccine (Wilkin *et al.*, 2010) .

In HIV-infected children and adolescents, data on the immunogenicity and safety of quadrivalent vcHPV are scarce. To date, few studies have been conducted. However, in a study of a cohort of HIV-infected children and adolescents aged 8 to 11 years, seroconversion for all 4 antigens was 96% higher among those who received quadrivalent vcHPV . In addition to being immunogenic, the vaccine was also shown to be safe (LEVIN *et al.*, 2010) .

Results from a multicenter study of 99 HIV-positive women aged 16 to 23 years indicated that immune responses to quadrivalent vHPV were robust and the vaccine was well tolerated. Seroconversion rates were 100% for HPV-6/11/16/18 among participants on antiretroviral therapy . Rates ranged from 92.3% (for HPV-18) to 100.0% (for HPV-6) among participants not on antiretroviral therapy . One serious adverse event (fatigue) was observed (Kahn et al., 2013) .

Australia, where the quadrivalent vaccine was implemented in the 2007 National Immunization Program and whose coverage rate was over 70% for the three doses in the target population, is now reaping the fruits of its initiative: a 92% reduction in the prevalence of HPV types 16 and 18 among women aged 18 to 35 (MACHALEK et al., 2018) ; a 90% reduction in genital warts in women aged 12 to 17 and 73% in women aged 18 to 26, in addition to a 38% reduction in men aged 18 to 26, indirect protection from vaccination exclusively for women (SMITH et al., 2015) . In Scotland, a significant reduction in diagnoses of cervical intraepithelial neoplasia was also observed in women who received three doses of the vaccine compared to unvaccinated women (POLLOCK et al., 2014) .

Although the literature indicates the high potential of the vaccine in preventing cervical neoplasia and genital lesions, vHPV has generated controversies that have an impact on acceptance and adherence by users (SILVA, OLIVEIRA and GALATO, 2019) .

In Brazil, a study conducted in 2002 assessed the knowledge and attitudes about HPV, cervical cancer and the Pap smear in 204 women aged 16-23 years, treated at a public hospital. The data revealed that 67% of the participants did not know that HPV can cause cervical cancer/warts and only 10% recognized that HPV could lead to cervical cancer (MOREIRA et al., 2006) .

Mendes Lobão and collaborators (2018 ) conducted a study to assess the acceptance of the HPV vaccine in Brazilian urban centers after its inclusion in the PNI. For daughters and sons up to 18 years of age, parental acceptance of the HPV vaccine was 92% and 86%, respectively. The study also revealed that those who refused vaccination were less likely to know that HPV is sexually transmitted and causes genital warts. In addition, prevention of cervical cancer and genital warts was less frequently cited by the parents surveyed as a reason for accepting the HPV vaccine. Although acceptance is high, there is no perception of the severity of the diseases for which the vaccine offers protection.

In a systematic review carried out with the aim of characterizing receptivity to the HPV vaccine and describing the barriers and facilitators of this receptivity, 11 facilitators and nine barriers to receptivity were identified. Knowledge about the vaccine stood out among the facilitators and the lack/inadequate information about the vaccine and the absence/low perception of the risk of infection were the most cited barriers (SILVA, OLIVEIRA and GALATO, 2019) .

### 3.4 THE THEORY OF MOTIVATION FOR PROTECTION

The Protection Motivation Theory (PMT) formed the theoretical basis of the intervention. According to her, when faced with information about a health threat, the motivation to protect oneself arises from the cognitive assessment of the severity of this threat (perceived severity), the perception of the probability of occurrence (perceived vulnerability), together with the belief that a recommended coping response can effectively prevent its occurrence (response efficacy) (Rogers, 1975) . According to Maddux; Rogers (1983) , an important variable that can affect the acceptance of a recommended coping response is the amount of work involved in its implementation (response cost). If an event is not assessed as serious, as likely, or as if nothing can be done about it, then no protective motivation would be aroused and, therefore, there would be no change in behavioral intentions (Rogers, 1975) .

Initially, the TMP postulated that the motivation for protection – and therefore the change in attitude – was a multiplicative function of these three mediating processes. Later, after its revision, the multiplicative notion was abandoned and the cognitive process of self-efficacy was included, that is, the belief that the person has the capacity to successfully execute the response to face the threat. Thus, the perceived severity, vulnerability Perceived and response effectiveness, in interaction with self-efficacy, determine intentions (protective motivation) to engage in a given behavior (MADDUX; ROGERS, 1983) . TMP has been used in several studies related to motivation for health protection (CAMERINI *et al.* , 2019; GAINFORTH, CAO and LATIMER-CHEUNG, 2012; GAINFORTH and LATIMER, 2012; MCREE *et al.* , 2018)

A study conducted in Switzerland with 554 parents of high school students aged 13 to 15 years used the principles of the PMT to identify predictors of parental intention to follow official MMR vaccination recommendations. Response efficacy

(vaccination) was shown to be directly related to parental intention to adhere to MMR vaccination recommendations (CAMERINI *et al.* , 2019) . The PMT was also used to predict hepatitis B vaccination intention and behavior in a population of adult immigrants in China. Perceived vulnerability and response efficacy were significant factors that determined hepatitis B vaccine acceptance (LIU *et al.* , 2016).

A study examined the theoretical determinants of HPV vaccination intentions by assessing the PMT and theory of planned behavior (TPB) constructs in three groups: college women, parents of daughters, and parents of sons. The results indicate that the PMT and TBP constructs predict intentions for the different groups. Focusing on vaccine response efficacy, rather than perceived HPV severity, was most effective in increasing vaccination intentions among all groups. Focusing on HPV vulnerability was effective only among college women and parents of sons, and self-efficacy predicted intentions among college women and parents of daughters (GAINFORTH, CAO, and LATIMER-CHEUNG, 2012) .

A pilot study to test an HPV vaccination intervention among 150 young gay and bisexual men aged 18 to 25 showed that HPV vaccination initiation was higher among those who received HPV information based on the PMT constructs (45% vs. 26%). This same group also showed a higher tendency to complete the full vaccination schedule (11% vs. 3%) (REITER *et al.* , 2018) .

### 3.5 THE USE OF MOBILE DEVICES FOR HEALTH INFORMATION

According to the 2017 TIC Households survey, which measures the availability and use of Information and Communication Technologies (ICT) in Brazil and is conducted by the Regional Center for Studies for the Development of the Information Society (Cetic.br), the number of Internet users in Brazil reached 120.7 million, representing 67% of the population aged ten or over. Of these, almost all (96%) used the Internet via cell phone, with 49% of them using the network only via this device (CETIC.BR, 2018) . The profile of exclusive use via cell phone was more common among users in classes D and E. and rural areas, reflecting a reality in which low-income citizens do not have multiple devices to access the Internet, as is the case in classes A and B. The survey also showed that 77% of Internet users access social

networks and 44% searched for information related to health or health services on the network in 2017.

Tozzi and colleagues (2010) used search engines to compare the quality of information about HPV and the HPV vaccine on *web pages* in both English and Italian. Scores in the domains of credibility, content, and design were higher on pages from public health agencies or universities. Some of the WHO-accredited websites in both Italy and the United States that include information about HPV immunization were not displayed by the search engines used in the study, suggesting that web pages *with* high-quality information about the HPV vaccine may not be easily retrieved by ordinary users. Most of the *web pages* displayed in this study were privately owned or news-provided websites, which typically host paid advertising or are for-profit.

A study carried out with MSM identified, through a focus group, that the increasing use of mobile strategies was identified as a facilitator for access to health information made available *online* (FONTENOT *et al.* , 2016) . Following this trend, American researchers carried out an intervention with MSM aged between 18 and 26 years old focusing on the use of mobile devices and found that, compared to participants in the control group, intervention participants reported a greater perception that MSM have a higher risk of anal cancer compared to other men, greater self-efficacy in vaccination against HPV and less perceived harm from using the vaccine (MCREE *et al.* , 2018) . At a time when misinformation circulates in large volumes in digital media, it is of utmost importance to have all the means to provide the population with useful and quality information in order to better guide decisions regarding the acceptance of vaccines.

An intervention study conducted to assess prior knowledge and the role of educational action on attitudes toward HPV vaccination in 200 women aged 18 to 30 years revealed that attitudes toward the HPV vaccine were different in the group that received the educational action. This group showed greater unconditional adherence to the vaccine, while the group without intervention conditioned acceptance of the vaccine to obtaining more information or to the recommendation of their attending physician. The researchers identified that only 28.6% of the participants had correct information about the preventive action of the HPV vaccine, and the majority (71.4%) believed that the vaccine had therapeutic purposes (PEREIRA *et al.* , 2016) .

Educational actions combined with mobile technologies and constructs that adequately motivate individuals to seek protection against health-related problems can increase the chances of success of vaccination promotion interventions.

## 4. OBJECTIVES

### 4.1 GENERAL OBJECTIVE:

To assess the feasibility, acceptability and effectiveness of a mobile-based intervention containing information about HPV and the HPV vaccine to promote vaccination in people living with HIV/AIDS.

### 4.2 SPECIFIC OBJECTIVES

4.2.1 Evaluate the effectiveness of the intervention by estimating:

4.2.1.1 Percentage of individuals intending to get vaccinated

4.2.1.2 Percentage of individuals who started vaccination

4.2.2 Determine the acceptability of the intervention with regard to:

4.2.2.1 Quality of information

*Website* quality

4.2.2.3 Usefulness of intervention

4.2.3 Analyze the feasibility of disseminating the intervention in the following strategies:

4.2.3.1 Poster / leaflet distribution

4.2.3.2 Social Media *Posts*

## 5. MATERIALS AND METHODS

This is an intervention study, a randomized controlled trial with PLWHA, divided into two groups. One of the groups will be presented with information about HPV and the HPV vaccine, prepared based on the Protection Motivation Theory (PMT). Another group will receive a clipping of information from the page maintained by the Ministry of Health dedicated to informing the population about HPV and the HPV vaccine. The materials for both groups will be delivered through two *websites* aimed at mobile devices ( *mobile friendly* ) with a common visual identity for the project. The “i-HPV” *website* , which will be displayed to the intervention group, and the “MS-HPV” *website* , which will be displayed to the control group.

### 5.1 SELECTION OF PARTICIPANTS

Recruitment will be carried out through two strategies: dissemination of printed invitations (posters and pamphlets) and *online invitations* ( *posts* on social media).

5.1.1 Printed invitations: Made possible by making pamphlets and posters available at locations that assist the key study population in the city of Salvador, Bahia.

5.1.2 Online invitations: For the free publication of posts on social media by institutions and organizations with good visibility and reputation aimed at disseminating issues of interest to PLWHA.

### 5.2 INCLUSION CRITERIA

- i. Living with HIV/ AIDS.
- ii. Age between 18 and 45 years.
- iii. Consent to participate in the study.

### 5.3 EXCLUSION CRITERIA

- i. Having taken any dose of the HPV vaccine.

Participants will be allocated in a 1:1 ratio using a computer algorithm. To prevent the allocation order from being discovered, the algorithm randomly allocates participants to one of the groups, but ensures that the difference in the number of participants in each group is no greater than five. Furthermore, given that the participant will likely access the system alone, we understand that this strategy will minimize the possibility of discovering the pattern used in the allocation and the chances of the participant circumventing the randomization.

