## 5.6 DATA COLLECTION

In both iHPV and MS-HPV, as soon as the participant starts browsing the “Get vaccinated” section, they will be asked about their intention to get vaccinated in the next three months. Their response will allow us to capture the primary outcome of the intervention. It also serves as a trigger for the start of the self-reported data collection phase.

It will be done in two ways: automatic collection via browsing data and questionnaire. In automatic collection, the origin and time of access to the pages will be recorded. Through questionnaires, sociodemographic data , intention to get vaccinated, evaluation of the intervention, and reasons for not getting vaccinated will be collected. All data will be collected electronically and saved in a database with restricted access to researchers.

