## 6.2 DATA ANALYSIS METHODOLOGY

A descriptive analysis of the frequency distribution of the main outcome variables and other variables will be performed. Continuous variables will be expressed as mean  $\pm$  standard deviation with a 95% confidence interval (CI), and categorical variables will be expressed as frequencies and percentages. To assess the effects of the intervention on the intention to get vaccinated (effectiveness), the groups will initially be assessed for sample homogeneity in relation to demographic and health-related characteristics. Differences between the groups studied will be calculated using *Student's t-test*. for quantitative variables and, for categorical variables, the comparison between groups will be performed using the Chi-square test. The logistic regression model will be used to compare the study groups in all outcomes, adjusting for potential confounding variables . Statistical analyses will be performed using the *software* Stata 12. P-values <0.05 will be considered statistically significant.

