### 6.2.3 Sample size

The goal will be to enroll 836 to 650 participants (assuming a 30% to 10% dropout rate) or 586 evaluable participants. By obtaining a sample of 293 evaluable patients per group and adopting a type I error probability (alpha) of 5%, we will have 80% power to detect a difference of 10% (20% vs. 30%) or greater between the intervention group and the control group.

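### Recruitment origin is logged automatically, but it is not used to balance allocation and is not named in the analysis; using it is a cheap, optional gain in balance and precision.

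*Protocol*

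**What the plan says.** Section 5.1 sets out two routes: "Recruitment will be carried out through two strategies: dissemination of printed invitations (posters and pamphlets"), placed at locations in Salvador that serve the study population, and posts on social media by organisations that address people living with HIV. Section 5.2 sets no geographic limit.

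Section 5.6 states: "In automatic collection, the origin and time of access to the pages will be recorded". Section 6.1.1 counts accesses to the home page (P0) by origin, and the stated use is the viability ratio for each type of invitation. Sections 5.4 and 5.5 show the arm-specific sites only after randomisation.

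The allocation paragraph in section 5.3 gives a 1:1 ratio and says that "the algorithm randomly allocates participants to one of the groups, but ensures that the difference in the number of participants in each group" does not exceed five. No stratification factor is named.

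Section 6.2 plans a chi-square test for categorical variables and a logistic model "adjusting for potential confounding variables", without a list. Its homogeneity check covers demographic and health-related characteristics and does not mention origin.

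**The concern.** The cap of five controls the arm totals and nothing else. One arm can by chance contain more people recruited online than the other. If readiness to be vaccinated differs between people reached through services and people reached through social media, such an imbalance moves the estimated difference away from its true value in that one trial. It also leaves variance in the comparison that could be removed.

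Origin is also useful for a practical reason. Under section 5.6 the intention answer triggers the questionnaire, so sociodemographic data are collected after the outcome and are missing for anyone who leaves before that point. Section 6.1.3 nevertheless divides by all participants randomised to each website. A model adjusted for questionnaire items would lose the early leavers from that denominator. Origin does not depend on reaching the questionnaire.

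Timing matters too. A covariate list can wait for a statistical analysis plan, but the allocation code must be settled before the first participant enters.

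**Working it through.** **Inputs from section 6.2.3.** The plan states "80% power to detect a difference of 10% (20% vs. 30%) or greater", a type I error of 5%, and: "By obtaining a sample of 293 evaluable patients per group". Sidedness is not stated; two-sided is assumed because it reproduces the figure.

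**The plan's own figure.** With pooled variance and no continuity correction,

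n = [1.96·√(2·0.25·0.75) + 0.842·√(0.2·0.8 + 0.3·0.7)]² / 0.10² ≈ 293.2 per arm,

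which is 294 rounded up, against 293 stated. Power at 293 is 79.98%. A one-sided test would need 231 per arm. The enrolment range also reproduces: 586/0.9 = 651 and 586/0.7 = 837, against 650 and 836 stated.

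**Assumptions.** The documents give neither the share recruited online (f) nor the gap in intention between routes (g). I take f = 50%, 70% or 90% and g = 0 to 20 points, and hold the overall rates at 20% and 30%.

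**Chance imbalance.** The SD of the between-arm difference in online share is √(2f(1−f)/293):
- f = 50%: √(0.5/293) = 4.1 points, 95% range ±8.1
- f = 70%: 3.8 points, ±7.4
- f = 90%: 2.5 points, ±4.9

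An imbalance of 1.96 SD moves the estimated difference by that imbalance times g. At f = 50% and g = 20 points this is 0.081 × 0.20 = 1.6 points, against a target of 10.

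**Precision of the risk difference.** Unadjusted, the variance is (0.16 + 0.21)/293, so the SE is √(0.37/293) = 3.55 points. Wald power is Φ(0.10/0.0355 − 1.96) = 80.3%. Within routes, p(1−p) falls by f(1−f)g² in each arm, so the numerator becomes 0.37 − 2f(1−f)g². At f = 50% and g = 20 points it is 0.37 − 0.02 = 0.35. The SE is then √(0.35/293) = 3.46 points and power is 82.5%. With arms balanced within routes, Mantel-Haenszel weights are proportional to route size, so this variance applies.

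| Online share | Gap (points) | Variance cut | Power | Shift at 1.96 SD (points) |
|---|---|---|---|---|
| 50% | 0 | 0% | 80.3% | 0 |
| 50% | 10 | 1.4% | 80.9% | 0.8 |
| 50% | 20 | 5.4% | 82.5% | 1.6 |
| 70% | 10 | 1.1% | 80.8% | 0.7 |
| 70% | 20 | 4.5% | 82.1% | 1.5 |
| 90% | 10 | 0.5% | 80.5% | 0.5 |
| 90% | 20 | 1.9% | 81.1% | 1.0 |

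At a 50:50 mix the variance cut is worth about 4 participants per arm with a 10-point gap and about 16 with a 20-point gap.

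**Scale.** The gain in precision is on the risk-difference scale. Take the 20-point case: 10% and 30% by route in the control arm, 20% and 40% in the intervention arm. The SE of the unadjusted log odds ratio is √(1/46.88 + 1/61.53) = 0.194. Combining the routes by inverse variance, with 146.5 per arm per route, gives about 0.201. The odds-ratio interval therefore widens.

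**The case against.** The strongest case against is that nothing in the plan is wrong. Randomisation without stratification is unbiased, and chance imbalance is already covered by the test's error rate and the interval. The 1.6-point shift is about 0.45 of a standard error, and it needs both a 1-in-20 imbalance and an assumed 20-point gap. With the larger numbers enrolled (325 to 418 per arm), the SD of the imbalance falls to 3.9 to 3.5 points. The 50:50 mix is the most favourable case for acting. All of this stands, and it is why the point is optional.

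Several stronger readings are tempting but not supported:
- **That origin is left out of the primary model.** Section 6.2 adjusts for unlisted confounders, so origin is neither in nor out, and the list may properly sit in an analysis plan that is not shown.
- **That origin is known for every participant before allocation.** This is a fair inference from sections 5.4, 5.6 and 6.1.1, but section 6.1.1 counts page accesses and does not say that origin is linked to a participant record or can always be classified.
- **That the two routes reach very different populations.** No figure supports this. Both routes target people living with HIV, and one person may meet both invitations.
- **That origin is the only covariate free of the questionnaire.** Time of access is logged with it.
- **That results by route serve the dissemination objective (4.2.3).** Section 6.1.1 measures that objective by access rates, not by effect within route.

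**Conclusion.** The point holds as a modest efficiency improvement. The allocation rule balances arm totals only, and origin, which the trial already logs, is not named as a stratifier or a covariate. Over assumed gaps of 0 to 20 points the gain in power runs from nil to about 2 points, and it shrinks as the mix becomes uneven. Protection against imbalance is worth at most about 1.6 points on the estimate at the 1-in-20 level. These figures rest on an assumed route mix, an assumed gap, and capture of origin before randomisation. A reader might infer bias or an error in the design; the documents show neither. The stated sample size reproduces and does not change.

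**What to change.** - **Section 5.3:** state that origin is stored for each participant at entry as printed, online or unknown, and run the same algorithm, with its cap of five, separately within each origin. This part must be decided before enrolment.
- **Section 6.2:** name as the primary comparison a Mantel-Haenszel risk difference for intention, stratified by origin, in all randomised participants, which matches the denominator in section 6.1.3. Any model using questionnaire covariates would then be supportive.
- **Optional:** show the effect within each origin, descriptively only. At a 50:50 mix there would be about 147 per arm per route, so these estimates would be imprecise.

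The cost is a small change to the allocation code, a per-participant origin tag carried over from the home page (feasibility to be confirmed), and a sentence or two of text. It needs no extra participants or questionnaire items. The overall arm difference may reach 10 with two origin groups, or 15 with three, instead of five; at this sample size that is immaterial.
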